## 7.1 Source Data Documentation

Source documents will include the following:

*Electronic questionnaire* — emailed to prospective participants who have given consent to be contacted in this way by providing their email address. The questionnaire will document whether or not a participant believes they meet the criteria for inclusion; whether or not they are willing to participate; and their availability for the consenting interview and scanning. It will also provide an option to provide

reasons for non-willingness to participate. By providing the name and address of their GP as well as their own postcode, prospective participants will be giving consent for their GP to be contacted.

*Consent to Participate Form* — to be completed by the participant with CI immediately prior to issue of the actigraphy wristband (7-10 days prior to scanning). Three copies must be signed by the participant and co-signed by the CI; one copy for the participant to keep, one copy to be added to the medical notes (sent to GP), and one copy for the Source Data File.

*Source Data notes in standardized hard copy File Note and Appointment Checklist formats* — on the day of scanning the CI will record participant ID, document willingness to participate, document any adverse events occurring since the consenting interview (and during the 7 days post-scanning), record confirmation of actigraphy wristband use (minimum 5 days) and ovulation (where applicable), record date, time, body weight, height, oral temperature, any deviations from or non-compliance with the Study Protocol or GCP, and any Serious Breaches.

*Image files* — MRI and MRS data will be stored on secure servers at Edinburgh Imaging prior to further processing.

*Actigraphy data files* – data will be identifiable only by unique participant number during collection and transfer via USB port to a secure University of Edinburgh computer. Data will be processed and used only if the participant proceeds with scanning, otherwise it will be safely destroyed.

## 7.2 Study Participant Data Forms

Source Data (participant ID, date, time, sex, DOB, height, weight, BMI, oral temperature, confirmed actigraphy recording and ovulation where applicable) will be carefully copied to a standardized paper-format SPDF template by the CI on the day of scanning. Completed SPDFs will be added to the Site File.

# 8 STATISTICS AND DATA ANALYSIS

## 8.1 SAMPLE SIZE CALCULATION

The sample size was estimated by a medical statistician ([name]) based on achieving the primary outcome using a linear mixed model for the analysis, and using previously published data exploring the reliability of MRS to measure  $T_{Br}$  in healthy human subjects. With a sample size of 36 subjects, and conservative true mean  $T_{Br}$  difference of 0.5°C for the primary outcome measure, there is 80% power to detect a statistically significant difference between time points at the 5% significance level. In total we aim to fully consent and scan 40 eligible participants to account for losses due to withdrawal, pertinent incidental HRFs that may require subject exclusion, and failed scans (e.g. technical failure of the scanner). A completion of a feedback pathway for 2 volunteers is expected (based on 5% prevalence of incidental HRFs using high-resolution MRI (see References). A 5-month recruitment period is considered entirely feasible to meet the required sample size.

## 8.2 PROPOSED ANALYSES

*Dependent variables* =  $T_{Br}$ ; oral temperature. Means and standard deviations will be reported

*Independent variables* = time of day; sex; BMI; chronotype; phase of menstrual cycle (for naturally cycling women); brain region (deep/superficial); duration of scan

The data collected during the course of this study is nested at several levels (participant, sex, chronotype, time of day, duration of scan etc), and as such, complex statistical modelling is required. The expertise of a medical statistician are critical to the analysis of the data; [name] will oversee and supervise all statistical analyses required for this study. A linear mixed model approach will be used to accommodate data incorporating repeated measurements per participant. A linear mixed model will account for the fact that  $T_{Br}$  measurements will be correlated within individuals in the analysis; it will also allow us to use data from all participants provided they undergo at least one, but not necessarily all 3 scans. This will ensure best use of participant and staff time.

HRF-based exclusion, and non-compliance with the Study Protocol will render the entire data set retrieved from a given individual unusable. The consequences of non-compliance are clearly explained in the Participant Information Sheet. Participants who are late for, or fail to attend, their first scan will be invited to reschedule their entire scanning day. Naturally cycling female participants who cannot demonstrate ovulation via urine test prior to their scheduled scanning day will be invited to reschedule urine testing and scanning for the following month.

The core analysis focuses on comparing mean  $T_{Br}$  between different time points across the cohort. Pre-defined subgroup analyses will include mean  $T_{Br}$  comparisons between men and women at each time point, and mean  $T_{Br}$  between deep and superficial brain regions at each time point.

Given the small scale of this study, interim analyses and reports are not appropriate. Additional volunteers will be recruited if sufficient eligible participants are not identified from the initial approach

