The second key decision was for the inclusion of female participants. Women were excluded from previous studies using MRS to measure  $T_{Br}$  in order to remove the potential confounding effect of the menstrual cycle on body (and possibly brain) temperature. We believe it is important, where possible, to include both sexes in studies of human brain physiology, such that the results of our study are as widely applicable as possible. Whilst it is well established that  $T_{Bo}$  can fluctuate during different stages of the menstrual cycle, and that there is a clear difference in chronotype between sexes at certain life stages, the primary outcome for this study is whether there is an intra-individual shift in  $T_{Br}$  between different times of the day. As such, each individual acts as their own control, and a linear mixed model approach can be used to address the effects of nesting at multiple levels when considering data within and between participants. It is also reasonably straightforward (and inexpensive) to control for chronotype differences (using activity monitors) and the effects of the menstrual cycle (by scanning all naturally cycling female participants at the same respective phase of their cycle i.e. post-ovulatory/luteal phase). Whilst this adds an additional non-invasive measurement (actigraphy) for all participants and an

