*Null hypothesis (2):* The variability in temperature within a single 24-hour period will not differ significantly between brain and oral regions of healthy human volunteers.

*Alternative hypothesis (2):* Human  $T_{Br}$  variation will exceed oral temperature variation within a single 24-hour period in healthy human volunteers.

There is conflicting data comparing brain and core body temperatures in humans and other animals, but generally,  $T_{Br}$  is considered to exceed core  $T_{Bo}$ , and we have recently observed a greater daily variability in  $T_{Br}$  relative to  $T_{Bo}$  in patients with traumatic brain injury (see References).

*Null hypothesis (3):* There is no statistically significant difference between brain temperatures measured in healthy men and women

*Alternative hypothesis (3):*  $T_{Br}$  will be higher in luteal-phase women and in women taking monophasic contraceptive medication compared to men, after accounting for chronotype differences.

It is established that an increase in progesterone during the post-ovulatory (luteal) phase of the menstrual cycle increases  $T_{Bo}$ , and there is published evidence that women in the luteal phase of their cycle have higher body temperatures throughout the circadian cycle relative to men. There is also evidence to suggest that the synthetic steroids (progesterone and oestrogen) provided in the monophasic contraceptive pill are associated with a persistently increased  $T_{Bo}$  throughout the cycle compared to the  $T_{Bo}$  observed during the natural follicular phase in women not taking oral contraceptives. We predict that this may also be reflected in  $T_{Br}$ , and therefore we would expect luteal-phase women and women taking monophasic contraception to have higher brain temperatures than men, irrespective of the time of the day.

*Null hypothesis (4):* There is no statistically significant difference between mean temperatures at the brain core and the brain surface in healthy human volunteers

*Alternative hypothesis (4):* Mean temperature at the brain core will be consistently higher than that at the brain surface, irrespective of time.

Intuitively, we would expect mean temperature deeper within the brain to exceed that at the brain surface, based on the laws of physics.

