The inclusion and exclusion criteria have been specifically developed to maximize participant safety, compliance, and wellbeing, whilst controlling for confounding effects that might impact upon  $T_{Br}$  and  $T_{Bo}$ , and/or thermoregulation generally. In particular,  $T_{Br}$  is highly dependent on blood flow to the brain, and on the sleep/wake cycle. We have therefore excluded people with known sleep disorders or with medical conditions that would be expected to affect general circulation, cerebral blood flow, or thermoregulation. Thermoregulation is also known to decline with age and is subject to variation in body mass, and so the age range has been limited to 20-40 years, and the BMI to 18.5-29.9. The proposed age range is consistent with the ages of healthy adult males recruited into the previously published study, and from which  $T_{Br}$  data was successfully acquired through MRS. The inclusion of women is a step forward from the previous study, which excluded women to avoid potential confounding effects of the menstrual cycle on  $T_{Br}$ . For the results of the prospective study to be widely applicable, it is important to include women whilst controlling for these effects. We believe that our approach is scientifically justified, easy to achieve, inexpensive, and logistically feasible within the duration of the study. We accept that for naturally cycling women there will be additional burden (urine testing in a location of their choosing, and a reduced selection of scanning dates) that may impact on their recruitment. However, we believe that this small impact is outweighed by the negative impact on recruitment if these women were to be excluded. Finally, the actigraphy data will allow us to control for differences in chronotype which are known to vary between the sexes, as well as between individuals of the same sex.

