#### *Procedures to detect and compensate for potential researcher bias*

- The first 20 men and 20 women that satisfy inclusion/exclusion criteria will be invited for a consenting interview; an additional 5 men and 5 women will be invited onto a 'stand-by' list and may be invited to attend for scanning if there are interim withdrawals or exclusions.
- Recruitment will close after 25 eligible men and 25 eligible women are identified, and will re-open only if necessary.
- Volunteers will be randomised to a single scanning weekday (according to their availability) within the 7-10 days following consent
- No subjects will be scanned on a weekend
- All MRS data processing will be performed blind to sex and time of day
- After processing is complete, the CI will be unblinded in order to perform data interpretation and statistical analysis
- Statistical analyses will be supervised by a medical statistician ([name])

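### Section 8.2 lists BMI but not age as an independent variable, so the male-female temperature comparisons are not adjusted for age (minor)

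*Protocol*

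**What the plan says.** Section 8.2 lists the independent variables as "time of day; sex; BMI; chronotype; phase of menstrual cycle (for naturally cycling women); brain region (deep/superficial); duration of scan". BMI is there and age is not.

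Section 3, in its reasoning for the design, treats the two factors as a pair: "Thermoregulation is also known to decline with age and is subject to variation in body mass". It gives that as the reason why "the age range has been limited to 20-40 years, and the BMI to 18.5-29.9".

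Section 7.2 shows that the data form carries "participant ID, date, time, sex, DOB, height, weight, BMI, oral temperature", so age can be derived for every participant.

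The comparison concerned is a pre-defined subgroup analysis in Section 8.2, "mean $T_{Br}$ comparisons between men and women at each time point". It is also the second secondary endpoint in Section 2.2.2, which covers oral as well as brain temperature, and hypothesis (3) in Section 3. That hypothesis names one adjustment only: "after accounting for chronotype differences".

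On selection, Section 3 says "The first 20 men and 20 women that satisfy inclusion/exclusion criteria will be invited for a consenting interview". No age matching or stratification is described.

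**The concern.** The protocol gives age and body mass the same standing as influences on temperature regulation and controls both by eligibility limits. It then carries only one of them into the analysis, and it does not say why restriction is enough for age but not for BMI.

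The omission matters where people are compared with other people. Sex cannot be randomised, and the two groups of 20 are filled separately in order of eligibility. If the men and women differ in mean age, and temperature varies with age between 20 and 40, a model without age assigns that difference to sex, except for whatever part BMI or chronotype picks up. What is at stake is the interpretation of hypothesis (3) and of the second secondary endpoint.

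**Working it through.** **What can be reproduced.** The only sample-size figure in the protocol (Section 8.1: 36 participants, 0.5 °C, 80% power, 5% level) concerns the contrast between time points. No standard deviation is given, so it can only be solved backwards. For a two-sided paired comparison, the implied SD of the within-person difference is 0.5 × √36 / (1.96 + 0.84) ≈ 1.07 °C. There is no power figure for the sex contrast and no age-temperature slope or correlation. Everything below about size is therefore an assumption.

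**Step 1. Which contrast is exposed.** For the time-of-day comparison Section 3 says "each individual acts as their own control". A stable effect of age cancels within a person, so the primary contrast does not depend on an age main effect. The sex contrast is between people and has no such protection.

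**Step 2. How far apart the mean ages could be by chance.** Assume ages uniform on 20-40 and 20 per sex.
- SD of age = 20/√12 = 5.77 years.
- SE of the difference in mean age = 5.77 × √(2/20) = 1.83 years, so the 95% range is about ±3.6 years.
- The chance that the difference exceeds 2 years is about 27%. The chance that it reaches 4 years is under 3%.

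**Step 3. What chance imbalance does to the test.** Under these assumptions, 100,000 simulated trials with no sex effect and no age adjustment gave a false-positive rate of 4.9% at a correlation of 0.3 and 4.9% at 0.5. Age variation is already part of the between-person variance in the standard error, so chance imbalance does not inflate the error rate.

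**Step 4. What a systematic difference does.** The shift in the sex contrast, in between-person SDs, is r × D / 5.77, where D is the fixed difference in mean age. The noncentrality is that shift divided by √(2/20) = 0.316. The false-positive rate follows from the noncentral t with 38 degrees of freedom.

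| D (years) | r | Shift (SD) | Noncentrality | False-positive rate |
|---|---|---|---|---|
| 2 | 0.3 | 0.10 | 0.33 | 6.2% |
| 2 | 0.5 | 0.17 | 0.55 | 8.3% |
| 4 | 0.3 | 0.21 | 0.66 | 9.8% |
| 4 | 0.5 | 0.35 | 1.10 | 18.7% |

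In degrees, with assumed slopes of 0.005 to 0.05 °C per year, a 4-year difference shifts the contrast by 4 × 0.005 = 0.02 °C to 4 × 0.05 = 0.20 °C.

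**Step 5. Precision.** The ratio of the adjusted to the unadjusted standard error is about √((1 − R²)(1 + 1/(N − 4))), where R² is the share of between-person variance explained by age.
- At R² = 0 the ratio is √(1 + 1/32) = 1.016 for N = 36 and √(1 + 1/36) = 1.014 for N = 40, so the interval widens by about 1.5%.
- Break-even is R² = 1/(N − 3): 1/33 = 3.0% for N = 36 and 1/37 = 2.7% for N = 40.
- At R² = 5%, 10% and 20% the ratio is about 0.99, 0.96 and 0.91.

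To put this as power, take a sex effect that has 80% power unadjusted with 20 per sex (0.909 SD, an assumed benchmark). Reduce the SD by √(1 − r²) and remove one degree of freedom. Power becomes 81.5% at r = 0.2, 83.5% at r = 0.3, 86.3% at r = 0.4 and 89.8% at r = 0.5. These figures are slightly optimistic, because they leave out the factor 1 + 1/(N − 4) for age not being exactly balanced between the sexes.

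**The case against.** The strongest reply is that the protocol already controls age by restriction. It limits age to 20-40 years because of the decline it mentions, and where it describes age effects (Sections 1.1 and 1.2) it speaks of aged or elderly people. Nothing in it says that temperature varies with age between 20 and 40. That caps the likely size of any bias and is a good reason to call the point minor. It does not remove the inconsistency, because BMI is restricted in the same sentence and is still listed.

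A second reply is that Section 8.2 lists variables without saying that all of them enter every model. The method summary in Section 1.2 mentions only time of day, chronotype and repeated measures, and the covariate set for a secondary contrast is often settled in an analysis plan. That is fair. But the protocol does state a list, and a plan that follows it inherits the omission.

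A third is that chronotype carries some information about age, since Section 3 links sex differences in chronotype to life stage. It may absorb part of an age effect, but it is not a substitute for age.

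Three stronger readings are tempting and are not supported:
- **Ordinary chance imbalance inflates the error rate to 10-19%.** It does not. The overall rate stays at about 5%, and those figures need a systematic 4-year difference. The documents show no such difference: both sexes are recruited through the same channels, with the same age limits and the same first-come rule.
- **Leaving age out necessarily costs precision.** Below about 3% of variance explained, adding age slightly widens the interval.
- **The primary analysis is compromised.** It is a within-person contrast and is not affected.

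**Conclusion.** The point stands as a minor one. Age is named as an influence on temperature regulation, is available at no cost, and is missing from a stated list that includes its companion BMI. The sex contrasts for brain and oral temperature are between-person and not age-matched, so an age difference between the sexes would be read as a sex effect.

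The size depends on figures the protocol does not give. With no systematic age difference, the false-positive rate stays at about 5%. With an assumed systematic difference of 4 years and an assumed correlation of 0.3 to 0.5 it would be about 10-19%, and with 2 years about 6-8%. The gain in power is modest at plausible low correlations (80% to 81.5% at 0.2, and to 83.5% at 0.3) and absent if age explains less than about 3% of between-person variance. The primary objective and its sample size do not change.

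**What to change.** In Section 8.2, add age (years, continuous, from date of birth) to the independent variables. Include it as a fixed effect in the mixed models for brain temperature and oral temperature that give the male-female contrasts. Report age by sex, so that a reader can see how far the groups differ. If the sponsor prefers to rely on the 20-40 restriction, the protocol should say why that suffices for age when BMI, also restricted, is still listed.

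The cost is one between-person degree of freedom and, if age turns out to be unrelated to temperature, a standard error about 1.5% wider. No new data, visits or participants are needed. It is better done now, because under Section 3 the chief investigator is unblinded before the statistical analysis, and a covariate added after that could look chosen on the results.

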#### 2.2.2 Secondary Endpoints

- The difference in variation of brain and oral temperatures across a 24-hour period

- The difference in brain and oral temperatures between men and luteal-phase women at each time point
- The difference between deep and superficial  $T_{Br}$  at each time point

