## 4.3 EXCLUSION CRITERIA

- Pregnant women
- Early menopause, irregular menstrual cycles, premenstrual syndrome, lack of luteinizing hormone surge (according to urine test) prior to two scheduled scanning days (women with natural menstrual cycles only)
- Body mass index < 18.5 or > 29.9
- Age < 20 years or > 40 years
- MRI contraindications (e.g. cardiac pacemaker, cochlear implant, claustrophobia, any prior accident in which metal penetrated one or both eyes)
- Oral temperature outside of normal range (33.2–38.1°C for women; 35.7–37.7°C for men) prior to any scan
- Medical history that might limit activity or alter cerebral blood flow (hypothyroidism, stroke, severe arthritis, Parkinson's disease, dementia, history of brain trauma, brain tumour or epilepsy, significant mental illness besides clinical depression, spinal cord injuries, recent serious burn, diabetes, dehydration)
- Taking medications (except seasonal allergy medication, over-the-counter NSAIDs, or contraceptives), acetaminophen (paracetamol), drug abuse
- Known neurodevelopmental, neuropsychiatric or neurodegenerative disorder
- Known sleep or chronotype disorder (delayed sleep phase syndrome (CRY1), familial advanced sleep phase syndrome (PER2))
- Known family history of cardiovascular disease at < 40 years of age
- Consumption of food or caffeine out with the specified time periods on the day of scanning
- Consumption of alcohol or participation in excessive physical activity on the day of scanning
- Failure to attend, or late attendance at, two independently scheduled morning scans

- Participant-reported ill-health on the day before or the morning of scanning

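### Section 8.2 lists a menstrual-phase variable that the design holds constant, omits contraceptive status, which varies, and the protocol defines the women in hypothesis 3 in three ways

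*Protocol*

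**What the plan says.** Section 8.2 gives the independent variables as "time of day; sex; BMI; chronotype; phase of menstrual cycle (for naturally cycling women); brain region (deep/superficial); duration of scan". The entry at issue is "phase of menstrual cycle (for naturally cycling women". The section gives no model formula and no coding.

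Section 3 controls the menstrual cycle by "scanning all naturally cycling female participants at the same respective phase of their cycle i.e. post-ovulatory/luteal phase". A woman whose ovulation is not confirmed is rescheduled to the following month (sections 3 and 8.2). Section 4.3 excludes naturally cycling women with "lack of luteinizing hormone surge (according to urine test) prior to two scheduled scanning days". Section 4.2 also admits women who have used monophasic contraception for at least three months.

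The comparison with men is worded in three ways:

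- Secondary endpoint (2.2.2): "between men and luteal-phase women at each time point". The matching objective in 2.1.2 also names luteal-phase women only.
- Alternative hypothesis 3 (section 3): brain temperature "will be higher in luteal-phase women and in women taking monophasic contraceptive medication compared to men". The supporting text expects this whatever the time of day.
- Section 8.2: brain temperature "comparisons between men and women at each time point", labelled a pre-defined subgroup analysis. The null for hypothesis 3 is also simply men versus women.

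**The concern.** A variable held at one value by design carries no information in the group it applies to. The distinction that does exist among the women, natural cycle versus monophasic contraception, has its own biological rationale in hypothesis 3 but no term in the variable list. With three definitions of the women's group, contraceptive users could be pooled with the luteal women, analysed separately or left out, and the protocol does not say which. Section 3 has the chief investigator unblinded before the statistical analysis, so an open choice here could be made with the data in view.

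There is also a mismatch of scope. Hypothesis 3 predicts a difference that does not depend on time, while the only sex comparison that 8.2 names is made separately at each time point. A single test of the hypothesis as worded would use all three scans. What is at stake is the meaning and precision of a secondary result.

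**Working it through.** **1. Can a phase effect be estimated?** Inputs: 20 men and 20 women (section 1.2), with k of the women naturally cycling. The protocol does not state k, so it was varied from 1 to 20.

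- Among the k naturally cycling women, phase is luteal for all. The intercept and phase columns are identical, so the matrix has rank 1 and there is no phase effect to estimate.
- If phase is left missing for everyone else, a complete-case fit keeps only those k women and the sex term is lost.
- If phase is coded luteal = 1 and everyone else = 0, write mean = a + b·sex + c·luteal. Men have a, contraceptive users a + b, and luteal women a + b + c. So b is contraceptive users minus men, c is luteal women minus contraceptive users, and luteal minus men is b + c. The rank is 3 whenever both female groups are present. With k = 20 the luteal and sex columns coincide and the rank falls to 2.

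**2. Precision of the contrasts**, as a standard error in units of between-subject SD:

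- All women v men: √(1/20 + 1/20) = 0.316.
- Luteal women v men, k = 10: √(1/20 + 1/10) = 0.387.
- Luteal women v men, k = 5: √(1/20 + 1/5) = 0.500.

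**3. The plan's own figure.** Section 8.1 gives 36 subjects, 0.5 °C, 80% power and a 5% level for the time-of-day comparison, with no SD. The figure can therefore only be solved backwards. For a paired two-sided test, SD of the difference = 0.5 × √36 / (1.960 + 0.842) = 1.07 °C by the normal formula, or 1.04 °C with the t distribution. The second gives a per-scan SD of 1.04/√2 = 0.74 °C. Other readings of the test put the SD of the difference between 0.93 and 1.21 °C, a per-scan SD of 0.66 to 0.86 °C.

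**4. Power for a women-v-men difference.** Assumptions: 18 men and 18 women; a true difference of 0.5 °C (the protocol gives this figure only for the time-of-day effect); two-sided 5%; scan SD s_w and between-person SD s_b.

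- SD of one scan = √(s_b² + s_w²). SD of the three-scan mean = √(s_b² + s_w²/3).
- With s_w = 0.74 and s_b = 0.3: √(0.09 + 0.548) = 0.80 and √(0.09 + 0.183) = 0.52.
- Power is from the noncentral t with 34 degrees of freedom and noncentrality 0.5 / (SD × √(2/18)).

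| s_w (°C) | s_b (°C) | One time point | Mean of three scans |
|---|---|---|---|
| 0.74 | 0.3 | 45% | 80% |
| 0.74 | 0.5 | 37% | 60% |
| 0.50 | 0.3 | 71% | 94% |
| 0.30 | 0.5 | 71% | 79% |

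Moving s_w over 0.66 to 0.86 with s_b = 0.3 changes the first row to 52% v 85% and 36% v 71%.

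**5. If only luteal women are compared with 18 men** (s_w = 0.74, s_b = 0.3, three-scan mean): 62% with 9 luteal women and 44% with 5. The second is no better than the pooled comparison at a single time point.

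**The case against.** A reader might infer that the listed model must either discard men and contraceptive users or fail to be estimable. The protocol does not support that. Section 8.2 is a list of variables, its bracketed qualifier confines phase to a subset of women, and it promises to use data from everyone with at least one scan. The luteal-versus-other coding is of full rank when both female groups are present, and coding is properly left to a statistical analysis plan. This stands. What it leaves untouched is that under such coding the terms labelled phase and sex no longer mean what their names say.

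A reader might also infer that hypothesis 3 will be tested only one time point at a time. The per-time comparison matches the secondary objective and endpoint, 8.2 says only that the subgroup analyses will include it, and sex is a listed variable, so an overall contrast is available. A difference at every time is also one reading of the hypothesis. The remaining defect is that no overall contrast is named for a hypothesis worded without regard to time.

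It may be tempting to settle the wording by making luteal women versus men the single test, as the endpoint suggests. That would drop the contraceptive users whom alternative hypothesis 3 includes, and at an unknown split it could lose most of the gain from averaging.

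Finally, the power figures rest on assumed SDs and a borrowed effect size. That is so, and they are offered only as an illustration.

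**Conclusion.** The point holds as an inconsistency in a secondary analysis. Menstrual phase is constant by design where it is defined, contraceptive status varies but is not listed, and the women's group has three definitions. These findings come from the text alone and need no assumed figures.

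The benefit of an overall contrast depends on assumptions the protocol cannot confirm. With 18 per sex and a 0.5 °C difference it is about 45% v 80% in the base case, clearly better in most settings tried, and small (71% v 79%) when between-person variation dominates scan error. The primary comparison is within person, so it and the sample size of 36 are essentially unaffected. The change should be made, but it does not threaten the main result.

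**What to change.** - In 8.2, replace sex and phase of menstrual cycle with one three-level factor: men; naturally cycling luteal-phase women; women on monophasic contraception.
- Use one definition of the women's group in 2.1.2, 2.2.2, hypothesis 3 and 8.2.
- For hypothesis 3, add one women-versus-men contrast averaged over the three scans and including both female groups. State how the two groups are weighted.
- Keep the per-time-point differences, and the separate luteal-versus-men and contraceptive-versus-men contrasts, as estimates with 95% confidence intervals.

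The cost is wording and one recorded field. Section 7 says the chief investigator knows in advance which women need urine testing, so contraceptive status is already known, but the participant data form fields in 7.2 do not list it. No new procedure or participant is needed. The separate contrasts will be less precise than the pooled one, by an amount that depends on the unstated split.
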